#### 2.1.2. Secondary Endpoints

To evaluate the local recurrence rate, pain control, quality of life and electrochemotherapy toxicity.

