### 2.6. Assessment of Efficacy

The response of treatment in both the control arm and the treatment arm will be assessed with the histopathological TRG on tissue specimens after local excision.

The total number of cases with TRG 1 and 2 [28] will be recorded and the proportion of responses will be compared between the two groups.

If the histological examination documents the presence of carcinoma with at least one of the following characteristics: 1. ypT ≥ 2; 2. Positive margins; 3. TRG > 2; 4. Poorly differentiated form (G3), the local excision will be considered inadequate treatment and the patient will undergo TME.

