### 2.8. Statistic Considerations

#### 2.8.1. Description of Sample Size Calculation and Planned Statistical Analyses

The sample size was determined by the Group-Sequential Superiority approach with a Margin Tests for the Difference of Two Proportions [36] using a complete response rate to the TRG after local excision as an endpoint. Sample size estimation has been carried out by using the superiority hypothesis in two independent parallel sample proportions [38,39,40,41,42]. According to the literature data, neoadjuvant chemo-radiotherapy treatment in LARC results in a complete response of 25% [43,44,45,46,47,48].

The proportion in the treatment group is assumed to be 0.25 under the null hypothesis and 0.50 under the alternative hypothesis. The proportion in the control group is assumed to be 0.25. The significance level of the one-sided test was targeted at 0.10 and the power at 80%.

An interim analysis will be conducted when 28 patients are enrolled (the percent of the sample size accumulated up to the corresponding look will be 40.0%). If a complete response rate to the TRG after local excision is noted in less than 25% of patients in the treatment group and/or feasibility/safety was not demonstrated, the study will be discontinued, otherwise a further 42 patients will be enrolled in the study.

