#### 2.8.2. Statistical Analysis

The treatment feasibility/safety of surgery following electrochemotherapy will be assessed considering the number of participants with compromised surgery following electrochemotherapy assessed by the R1 resection rate, circumferential resection margin (CRM) involvement, non mesorectal resection plane, and post-operative complications according to the Clavien-Dindo Classification. A surgical complications rate of 30–40% was reported in the literature for conventional neoadjuvant treatment followed by TME [37]. The evaluation of each arm will be performed at Visit 5 (12 weeks from ECT/8 weeks from LE).

Complete response rate (TRG 1 and 2), disease recurrence rates and percentages will be compared among the two groups. A one-sided Fisher exact test will be performed to test the differences between the groups. Differences will be considered significant at *p* < 0.10. A Chi square test will be performed to assess statistically significant differences among the groups for the categorical variable.

The time interval between the recruitment date and local disease progression will be represented using the time of treatment failure and median and minimum–maximum values will be considered.

The scores obtained by the QOL, pain and satisfaction questionnaires will be evaluated. Any serious adverse events and their intensity, according to the NCI-CTCAE classification (version 5.0), will be registered in the first two days post-procedure.

Mean ± standard deviation will be considered for normally distributed continuous variables while the median and interquartile range (IQR) will be presented for non-normally distributed continuous variables.

For continuous variables, the difference between follow-up values and baseline values will be tested by a 2-sided Student t-test or by a Mann–Whitney test while, for the categorical variables, the McNemar test and the marginal homogeneity test will be use [49,50].

Time to event outcomes will be analyzed using the Kaplan–Meier method and survival curves will be compared using the log-rank test.

Mixed effect regression models will be used to analyze longitudinal data by adjusting for proper covariates.

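### Disease recurrence is put under the one-sided Fisher test built for response, with no direction stated and no rule on which of three listed tests governs it

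*Protocol article*

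**What the plan says.** All references are to the protocol article.

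- Section 2.1.2 makes recurrence a secondary endpoint: "To evaluate the local recurrence rate, pain control, quality of life and electrochemotherapy toxicity".
- Section 2.8.2 groups it with the response endpoint: "Complete response rate (TRG 1 and 2), disease recurrence rates and percentages will be compared among the two groups". The next sentence gives the test: "A one-sided Fisher exact test will be performed to test the differences between the groups". The threshold follows: "Differences will be considered significant at" p < 0.10. No direction is given for either outcome.
- Section 2.8.1 supplies a direction for response only: "The proportion in the treatment group is assumed to be 0.25 under the null hypothesis and 0.50 under the alternative hypothesis", with "The proportion in the control group is assumed to be 0.25". It also sets the level: "The significance level of the one-sided test was targeted at 0.10 and the power at 80"%.
- Section 2.8.2 then lists a chi-square test for categorical variables. Further on it lists Kaplan–Meier curves with a log-rank test for time-to-event outcomes, and it describes a time from recruitment to local progression. Neither test is called one-sided, and the section does not say which of the three applies to recurrence.
- The discontinuation rules in Section 2.8.3 cover response, feasibility/safety, adverse events and surgical complications. They do not name recurrence.

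**The concern.** A one-sided test answers a question in one direction. For response the direction is clear and the choice is reasonable. For recurrence the stated aim is to test differences, and either direction would be of interest. ECT might reduce recurrence by clearing residual disease. It might also increase it: under Section 2.6, a specimen with TRG above 2 is one of the findings for which "the local excision will be considered inadequate treatment and the patient will undergo TME", so if ECT moves more patients to TRG 1 or 2, more of them may keep the mesorectum.

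A one-sided test with no stated direction leaves two problems. Whichever direction is chosen, an effect the other way cannot be declared. And because the direction is not fixed, it could be chosen after the data are seen. With two further tests listed and no order among them, the report could pick from results that disagree, on an outcome that bears on the organ-sparing claim.

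**Working it through.** **The plan's own figure.** The design is one-sided for response. Inputs (Section 2.8.1): 0.25 v 0.50, one-sided alpha 0.10, power 80%. With pooled variance under the null and mean proportion 0.375:

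n per arm = [1.2816 × √(2 × 0.375 × 0.625) + 0.8416 × √(0.1875 + 0.25)]² / 0.25² = (0.8774 + 0.5567)² / 0.0625 = 32.9, so 33 per arm.

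A two-sided test at 0.10 would need 46 per arm. Allowing for one look at 40% brings the total to between 68 (O'Brien–Fleming-type spending, pooled variance) and 72 (Pocock-type spending, unpooled variance), so the planned 70 is reproduced. The one-sided choice is thus part of the response design. Nothing comparable is set out for recurrence.

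**One data set, three tests.** Take 35 per arm (70 patients, 1:1) and suppose 10/35 recurrences on ECT and 3/35 on control. Given 13 recurrences in total, the ECT count is hypergeometric (70 patients, 13 events, 35 drawn).

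- One-sided Fisher, alternative of less recurrence on ECT: P(X ≤ 10) = 0.994.
- One-sided Fisher, alternative of a higher ECT proportion: P(X ≥ 10) = 0.031.
- Two-sided Fisher: 2 × 0.0312 = 0.062 (the distribution is symmetric because the arms are equal).
- Chi-square without correction: pooled proportion 13/70 = 0.1857; z = 0.20 / √(0.1857 × 0.8143 × 2/35) = 0.20 / 0.0930 = 2.15; p = 0.031 (0.065 with Yates correction).

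At 0.10 the benefit-directed Fisher test reports nothing, while the chi-square reports a significant excess. If the arms are swapped (3/35 on ECT, 10/35 on control), a Fisher test directed at a higher ECT proportion gives 0.994 for what is then an apparent benefit.

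**How often this matters.** The protocol gives no recurrence rates, so those below are assumptions. Every pair of counts for 35 v 35 was enumerated, weighted by its binomial probability, and counted when p < 0.10. All recurrences are assumed to be ascertained.

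| Control v ECT | One-sided Fisher, benefit direction: any rejection | Same test: flags excess | One-sided Fisher, harm direction | Two-sided Fisher, flags excess | Two-sided chi-square, flags excess |
|---|---|---|---|---|---|
| 5% v 20% | 0.02% | 0 | 65% | 45% | 63% |
| 10% v 25% | 0.06% | 0 | 54% | 38% | 50% |
| 10% v 30% | 0.01% | 0 | 72% | 58% | 68% |

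The few rejections in the second column favour ECT wrongly, so none of them signals harm. The two-sided Fisher column changes only the sidedness. The chi-square column changes the test as well, so the gap it shows is not due to sidedness alone.

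**The case against.** A reader might infer that the plan cannot detect more recurrence on ECT. The documents do not support that.

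- The direction for recurrence is not written down. Reading superiority as less recurrence on ECT is natural, and the Discussion links complete pathological response to fewer local recurrences, but it remains an inference. If the stated alternative for response (higher ECT proportion) is carried over literally, the test looks for harm.
- The same section lists a chi-square test, which has no direction, for categorical variables. Recurrence yes/no is categorical. It also lists a log-rank test that is not called one-sided. Either could show an excess, so the plan as a whole is not blind to harm.
- A reader might also take recurrence to be the main oncological risk peculiar to the ECT arm. That is a judgement and not in the text. Both arms have local excision, and Section 2.6 states its criteria for TME without distinguishing the arms. The arms differ in organ sparing only if ECT shifts TRG.
- Recurrence is an unpowered secondary endpoint in a 70-patient phase II trial, and the observed rates would be visible whatever the p-value.

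These points limit the size of the concern but do not remove it. The one-sided Fisher sentence directly follows the sentence that names recurrence, so the rule is stated and is not a detail left to an analysis plan. The extra tests add a second problem, because they can contradict the Fisher test and no order is given. Low power is a reason to report an estimate with an interval rather than a one-sided p-value.

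**Conclusion.** The point holds as a mismatch and an ambiguity: a stated one-sided rule is applied to an outcome for which no direction is given or justified, alongside two other tests with no precedence. The wrong-direction result is certain once a direction is chosen, since a one-sided test never declares the opposite effect.

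In the three assumed scenarios, moving from a benefit-directed one-sided Fisher test to a two-sided Fisher test raises the chance of flagging an excess from zero to between 38% and 58%. With a two-sided chi-square the range is 50% to 68%. It would be tempting to quote a loss of 50 points or more. That holds in all three scenarios only if the test is also changed to chi-square; on sidedness alone it holds in one of the three. All these figures rest on the assumed rates, 35 analysed per arm, full ascertainment and the benefit-directed reading. The primary response comparison and the sample size are not affected.

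**What to change.** In Section 2.8.2, limit the one-sided Fisher test at 0.10 to TRG 1 and 2 response. For recurrence, name one two-sided analysis and state that it governs: either the ECT minus control difference in proportions with a two-sided 90% confidence interval, or a two-sided log-rank test with the hazard ratio and its interval. Say that the chi-square test listed there does not also apply to recurrence.

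This takes a sentence or two and needs no extra patients or data. The cost is that lower recurrence on ECT becomes somewhat harder to declare than with a benefit-directed one-sided test. By symmetry (arms swapped in the table), the power falls from 65%, 54% and 72% to 63%, 50% and 68% if a chi-square-type analysis is used, and to 45%, 38% and 58% with a two-sided Fisher test. On a secondary endpoint with no stated power, that is a small price, and it favours the interval over the exact test.

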## 2. Trial Design

Seventy patients will be enrolled in a Phase II randomized controlled trial. The study will be developed in two stages. In the first step, 28 patients will be enrolled: 14 of these will receive ECT for four weeks after neo-adjuvant treatment and then local excision (treatment group) and 14 patients will receive neo-adjuvant treatment and then local excision (control group). Electrochemotherapy will be performed with the CLINIPORATOR™ and an intravenous dose of Bleomycin. If an increase of response rate is observed in the first stage and/or feasibility/safety is demonstrated, the second stage of the trial will be performed. In the second step, an additional 42 patients will be enrolled and treated. Trial design flow-chart is showed in Figure 1.

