### 2.2. Subject Selection

Eligible patients will be randomly assigned (1:1) to the treatment group or the control group. The treatment group assignment will be assigned blindly and sequentially in the order in which eligible patients are enrolled in the study. Patients eligible for inclusion in the protocol (see Table 1) will be informed in detail about the study and, if they consent to participate, they will sign the informed consent form (Appendix A), witnessed by a member of the research group.

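### The planned one-sided Fisher exact test with 35 patients per arm has about 73% power, not the stated 80%

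*Protocol article*

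**What the plan says.** All inputs are in the protocol article.

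- **Size and allocation.** Section 2: "Seventy patients will be enrolled in a Phase II randomized controlled trial". Section 2.2: "Eligible patients will be randomly assigned (1:1) to the treatment group or the control group". Together these give 35 per arm.
- **Sizing method (section 2.8.1).** The size comes from a "Group-Sequential Superiority approach with a Margin Tests for the Difference of Two Proportions". The test statistic, the margin and the boundary are not given.
- **Rates (section 2.8.1).** "The proportion in the treatment group is assumed to be 0.25 under the null hypothesis and 0.50 under the alternative hypothesis", and "The proportion in the control group is assumed to be 0.25".
- **Error rates (section 2.8.1).** "The significance level of the one-sided test was targeted at 0.10 and the power at 80" per cent.
- **Analysis (section 2.8.2).** Immediately after naming complete response (TRG 1 and 2) and recurrence as the quantities to compare, the protocol says: "A one-sided Fisher exact test will be performed to test the differences between the groups". The threshold follows: "Differences will be considered significant at *p* < 0.10". A chi-square test for categorical data comes next, without saying which variables it covers.
- **Interim (sections 2.8.1 and 2.8.3).** After 28 patients (14 per arm), the trial stops if fewer than 25% of treated patients respond, or if safety or feasibility is not shown.

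**The concern.** The power claim and the test that must deliver it are both fixed in the text, in adjacent subsections, so this is not a detail left to an analysis plan. Fisher's test conditions on the total number of responders. With arms of 35 its p-values move in coarse steps, and its true error rate falls well below the nominal level. A size derived for an approximate z-test therefore does not carry over to it.

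The design accepted a lenient one-sided 0.10 so that 70 patients would be enough. If the test cannot use that allowance, the risk of missing a true doubling of response is about 27%, not the planned 20%. That risk falls on the endpoint used to size the trial.

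**Working it through.** **Inputs:** 35 per arm; control 0.25; treatment 0.50; one-sided α = 0.10 (z = 1.2816); power 80% (z = 0.8416).

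**1. Where 70 comes from.**

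Fixed-design normal approximation, n per arm:

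- Unpooled variance: (0.25×0.75 + 0.50×0.50) × (1.2816 + 0.8416)² / 0.25² = 0.4375 × 4.508 / 0.0625 = 31.6.
- Pooled variance under the null (mean rate 0.375): [1.2816×√(2×0.375×0.625) + 0.8416×√0.4375]² / 0.25² = (0.8774 + 0.5567)² / 0.0625 = 32.9, so 33 per arm.

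Pooled formula power at 35 per arm: Φ[(0.25×√35 − 0.8774) / √0.4375] = Φ(0.9095) = 81.8%.

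Adding a second look at 40% information, with an O'Brien-Fleming-type boundary (my assumption) and pooled variance, gives 79.9% at 34 per arm and 80.8% at 35. That reproduces 70 patients. A Pocock-type boundary gives 77.5% (pooled) or 79.7% (unpooled) at 35. With a continuity correction, which mimics Fisher's test, the fixed design needs 41 per arm.

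**2. Power of the test named in section 2.8.2.**

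Let X_T ~ Bin(35, 0.50) and X_C ~ Bin(35, 0.25). Power is the sum of P(X_T = t) × P(X_C = c) over every one of the 36 × 36 outcomes with one-sided Fisher p < 0.10. Size is the same sum with both rates equal.

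For the interim stop, fewer than 25% of 14 means 3 or fewer responders. The probability of stopping is P(Bin(14, 0.50) ≤ 3) = 2.9% under the alternative and 52.1% under the null.

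| Test, 35 per arm | Power | Power with interim stop | Size at 0.25 | Maximum size |
|---|---|---|---|---|
| Fisher exact | 73.8% | 72.8% | 6.4% | 6.6% |
| Pooled z (uncorrected chi-square) | 80.9% | 79.6% | 10.3% | 11.9% |
| Boschloo | 80.2% | 79.0% | – | 9.6% |
| Fisher mid-p | 80.2% | 79.0% | – | 9.8% |

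Sizes are without the stop; the stop lowers Fisher's size at 0.25 to 5.2%.

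**3. Size of the shortfall.**

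- Power: 80 − 73.8 = 6.2 points, or 80 − 72.8 = 7.2 points with the stop.
- Unused error: (10 − 6.4) / 10 = 36% of the allowance.
- Fisher's test first reaches 80% at 40 per arm (80.1%, 80 patients). With the stop it does so at 41 per arm (80.0%, 82 patients). That is 10 to 12 more patients than planned.

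**4. An outcome where it matters.** With 15/35 responders on treatment and 9/35 on control, Fisher's p is 0.104, which fails. The mid-p value is 0.071, and Boschloo's test also rejects.

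**The case against.** The arithmetic is not in dispute. The case on the other side has five parts.

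- **The cause is inferred.** The protocol never calls its sizing test asymptotic, and reproducing 70 exactly needs an assumed boundary. This stands as a caution about the explanation. It does not touch the shortfall, because Fisher's power at 35 per arm is 73.8% however 70 was reached.
- **Fisher's test is valid and buys error control.** This is true against the uncorrected z-test, whose size reaches 11.9%. It is no advantage that the trial needs over Boschloo's test, which is also exact and stays within 10%.
- **The loss is modest.** Fisher's test reaches 80% without the stop if the true treatment rate is 52.5% rather than 50%, and both assumed rates are uncertain. No false positive or bias results. That is fair, but the protocol states 80% at 50%, and at that rate the figure is wrong.
- **The chi-square test is not assigned to TRG response.** This is also fair. The wording is ambiguous rather than contradictory, so what is needed there is clarification.
- **The alternative tests also fall just short with the stop, at 79.0%.** This is correct and should be stated openly. The gap is then one point instead of seven.

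**Conclusion.** The concern holds. With the protocol's own inputs, the test it names has 73.8% power, or 72.8% with the interim response stop, against a stated 80%. Its actual one-sided error is 6.4% (at most 6.6%) against a nominal 10%. The fault is a mismatch between the sizing in section 2.8.1 and the analysis in section 2.8.2. The 80% figure itself is reproducible for a z-type test.

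The calculation assumes a zero superiority margin, no early stop for efficacy, exactly 35 evaluable patients per arm, and only the response part of the interim rule. Dropout or a safety stop would lower power further. That the size came from an asymptotic test is a well-supported inference, and the conclusion does not depend on it.

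**What to change.** In section 2.8.2, name one primary test of TRG response before any unblinded response data are seen. Any of these removes the mismatch:

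1. **Preferred:** a one-sided Boschloo unconditional exact test at 0.10, or Fisher mid-p. Power is 80.2%, and the protocol should say that it is 79.0% with the interim stop. Boschloo's test holds its level by construction. For mid-p the 9.8% maximum was checked at 35 per arm and should be rechecked if the final arm sizes differ.
2. **Keep Fisher's test and 70 patients,** and restate the power as about 73%.
3. **Keep Fisher's test and 80% power,** and enrol 80 patients, or 82 allowing for the interim stop.

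In each case, state that the chi-square test does not apply to TRG response, so that one endpoint does not have two tests that can disagree. The uncorrected chi-square is not a safe substitute, because its one-sided size exceeds 10%.

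Options 1 and 2 cost a sentence or two and no patients. Option 3 costs 10 to 12 patients.

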### 2.4. Duration of the Study and Follow up

The study will last 36 months with five follow-up years for all patients enrolled. The time for enrolment will be 36 months.

Patients after local excision will be visited every three months in the first two years, and then every six months in the following three years.

This study is subject to stopping rules. Patients can decide to interrupt the treatment. Subjects who discontinue/withdraw from study participation will be evaluated by study personnel.

Starting from the informed consent signature, any event occurring during the treatment phase and/or the follow up phase, will be considered an Adverse Event (AE) and will be recorded. Any clinical or biological abnormalities not present at the trial start will be considered intercurrent events.

The visits scheme is summarized in Table 2.

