### 2.7. Assessment of Feasibility/Safety

Any Adverse Event (AE) will be recorded on the case report form as well as the intercurrent events. Subjects will be examined at each visit or if the subject reports any unusual symptoms. The numbers and severity of such incidents will be included in the statistical analysis. All Adverse events (AEs and SAEs) will be recorded on the AE form. Serious adverse events (SAEs) will be reported to the IRB. Toxicity will be assessed using the National Cancer Institute’s Common Toxicity Criteria for Adverse Events, version 5.0 (CTCAEv5) [32].

A collection of adverse events will be conducted at Visit 2 to individuate the AE rate due to neoadjuvant treatment. Neoadjuvant therapy is usually well tolerated, although some patients can require hospital admission for the management of diarrhea or significant late small bowel toxicity, attributable to radiotherapy [33,34,35,36,37].

A following collection of adverse events will be conducted at Visit 3, before LE, to individuate the AE rate due to added treatment (ECT).

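### Section 2.8.2 registers SAEs in the two days after an undefined procedure, which conflicts with the recording and analysis periods in 2.4 and 2.7

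*Protocol article*

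**What the plan says.** Four parts of the protocol article bear on which adverse events are recorded and analysed.

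- **2.8.2, Statistical Analysis.** Serious adverse events and their CTCAE version 5.0 intensity "will be registered in the first two days post-procedure". The index procedure is not named.
- **2.4, Duration of the Study and Follow up.** "Starting from the informed consent signature, any event occurring during the treatment phase and/or the follow up phase" counts as an adverse event and is to be recorded.
- **2.7, Assessment of Feasibility/Safety.** "All Adverse events (AEs and SAEs) will be recorded on the AE form", and "The numbers and severity of such incidents will be included in the statistical analysis". Neither sentence has a time limit. The section then separates two collections: one at Visit 2 for events due to neoadjuvant treatment, and a later one for ECT: "A following collection of adverse events will be conducted at Visit 3, before LE, to individuate the AE rate due to added treatment".
- **2.5, Description of Study Procedures.** The text for Visit 4 and for the follow-up visits through Visit 18 provides for recording adverse events and complications.

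Two further provisions set the context. Section 2.8.2 separately judges the feasibility and safety of surgery by R1 rate, circumferential margin, resection plane and Clavien-Dindo complications, evaluated at Visit 5 (12 weeks from ECT, 8 weeks from LE). Section 2.8.3 makes a 20% difference between arms in AE rate and surgical complications rate a reason to discontinue, and names no time window for either rate.

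**The concern.** The protocol gives two observation periods for SAEs, and the narrow one stands in the section an analyst will follow. The sections do not say which prevails.

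The missing definition of the procedure makes this worse. Only the treatment arm has ECT; both arms have LE. The sentence can therefore mean three different things, and none of them gives a window that is the same in both arms and also covers the ECT-to-LE interval from which 2.7 takes ECT toxicity.

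Feasibility/safety of ECT is the first primary endpoint (2.1.1) and ECT toxicity is a secondary endpoint (2.1.2). At stake is which SAEs enter the toxicity analysis and report. If the choice of window stays open until data are in hand, it could be made with knowledge of the results.

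**Working it through.** The plan states no figure to reproduce here. The check sets the two-day window against each safety interval that the protocol itself defines.

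**Inputs**

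- Registration window: 2 days (2.8.2).
- ECT at Day 0, LE at Day 30 ± 3 (2.5.3 and Table 2): 30 days, range 27 to 33.
- LE to Visit 5: 8 weeks = 56 days (2.8.2).
- ECT to Visit 5: 12 weeks = 84 days (2.8.2).

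**Formula:** share covered = 2 / length of interval in days.

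- ECT to LE: 2/30 = 6.7% (2/33 = 6.1% to 2/27 = 7.4%).
- LE to Visit 5: 2/56 = 3.6%.
- ECT to Visit 5: 2/84 = 2.4%.

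If the day of the procedure is counted in addition to the two following days, the first figure becomes 3/30 = 10.0%.

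**The three readings of the procedure**

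| Reading | ECT-to-LE interval, treatment arm | Control arm | Same window in both arms? |
|---|---|---|---|
| ECT | 2 of 30 days (6.7%) | no window | no |
| LE | none | 2 days after LE | yes, but ECT-to-LE is uncovered |
| Both | 2 of 30 days, plus 2 days after LE | 2 days after LE only | no |

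Under 2.4 and 2.7 as written, by contrast, nothing in these intervals is left uncovered.

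**Visit schedule.** In Table 2 the visit after Day 0 is Day 30 ± 3, and the one after that is Day 37 ± 3. No scheduled visit falls at two days after ECT or two days after LE.

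**Interim rule, only if the two-day window were applied to it.** The interim look has 14 patients per arm (Section 2). With no events in the control arm, two treatment-arm patients with an event give 2/14 = 14.3% and three give 3/14 = 21.4%. One patient whose event falls inside or outside the window can therefore move the difference across 20%.

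**The case against.** The strongest defence is that the two-day sentence excludes nothing. It does not say that SAEs are registered only in those two days, and it can be read as an extra peri-procedural registration on top of the general recording. Section 2.7 requires every SAE on the AE form and says, without a time limit, that numbers and severity enter the analysis. That is itself an analysis statement, so later SAEs are collected and arguably analysed. This stands as far as collection goes: the protocol as written does not lose later events. It does not settle the analysis, because nothing in 2.8.2 marks the sentence as additional.

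A reader might infer more than the text supports, in four ways.

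- *That the safety endpoint as a whole misses most of its risk period.* The surgical feasibility/safety assessment runs to Visit 5 and includes Clavien-Dindo complications, so a delayed complication of LE is still counted there. The ECT AE rate is taken at Visit 3. Neither is tied to two days.
- *That the interim stopping rule is distorted.* Section 2.8.3 does not refer to the two-day window.
- *That the arms necessarily have different windows.* With LE as the anchor they are the same.
- *That ECT would look safer than it is.* Dropping late ECT events would act in that direction, but an ECT anchor leaves controls with no window, and anchoring on both procedures observes the treatment arm for longer. Either could make ECT look worse. The direction depends on the reading.

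The percentages are also shares of calendar time. The documents give no distribution of SAE timing, so they do not show what share of SAEs would be missed.

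**Conclusion.** The inconsistency is real and lies in the current text: 2.8.2 gives a two-day SAE window around an unnamed procedure, while 2.4 and 2.7 give recording and analysis without that limit. It is a rule stated badly, not detail left to an analysis plan.

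The consequence is conditional. If the two-day sentence governs the SAE and toxicity analysis, about 93% of the ECT-to-LE interval falls outside it with an ECT anchor (100% − 6.7%), and all of it with an LE anchor. With an ECT anchor the control arm has no window for comparison. If 2.7 governs, nothing is lost.

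The conclusion is therefore confined to SAE and toxicity analysis and reporting, and extends to the interim AE rate only if the same window is used there. It rests on the nominal 30-day interval (27 to 33 days changes little) and makes no claim about the number of events missed or the direction of bias.

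**What to change.** 1. In 2.8.2, either delete the two-day limit or label it as an additional peri-procedural summary. If it is kept, name the index procedure for each arm.
2. State that SAEs and graded AEs are analysed over windows that are the same in both arms, for example Day 0 to LE and LE to Visit 5, with later SAEs listed through follow-up. This brings 2.8.2 into line with 2.4 and 2.7. Other common windows would also serve, provided they cover the interval that 2.7 uses for ECT toxicity.
3. Say what Day 0 is for controls. Table 2 places Visit 2 at Day 0 but describes it only by the treatment group's ECT; using the Visit 2 date in both arms would do, assuming controls attend that visit.
4. In 2.8.3, tie the AE rate to one of these named windows.

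The cost is a few sentences, best added before the interim look. No new data collection is needed, because 2.5 and 2.7 already provide for adverse events to be recorded at these visits.
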